Power analysis is used to estimate the sample size estimation for pre-test–post-test study with attrition [15]. According to two pilot-scale studies which examined the effects of moderate-intensity endurance exercise on sleep among older adults [11, 13], the effect sizes of exercise interventions on sleep quality and pattern were in the range of 0.21–1.55 (Cohen’s d). Hence, this study aims to detect a small to medium effect size of 0.4 on the primary sleep pattern and quality outcomes. Using the program RMASS2, it is estimated that a sample size of n = 104 participants per study arm would give the study 80% power at a 5% level of significance to detect the targeted effect size of exercise, assuming randomization will render the two arms equal at baseline and allowing for a 10% attrition. As this study also aims at examining the mediating process between exercise and sleep, consideration is also given to the sample size requirement for path analysis using structural equation modeling approach. According to Loehlin, a sample size of at least 100 and preferable ≥ 200 is required to ensure the statistical power for conducting structural equation modeling [16] and thereby increasing the sample size to 112 individuals per study arm, in allowing for a 10% attrition, to attain the recommended total sample size of 200 participants (i.e. 112 × 0.9 = 100 per arm).

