**Fig. 3 Fig3:**
[figure not shown]
The SPIRIT figure

Block randomization with a block size of about 20 using a restricted shuffled approach will be used to ensure an even distribution of individuals among the study arms. The randomized block is based on the time sequence of participant recruitment. Whenever an individual is being recruited, a consecutively coded number (i.e. participant code number) will be assigned to him/her according to the time sequence of recruitment. After the baseline data collection, the first 20 individuals being recruited (e.g. participant code numbers 1–20) will be evenly randomized to the study arms in a block. A computer-generated random sequence determines the group assignment of these 20 individuals. Twenty paper cards labelled with “exercise” or “control,” with each placed in a single sealed opaque envelop, will be arranged in an order to represent the generated sequence. These envelopes will be numbered consecutively according to this specified order and distributed to the 20 participants according to the participant code sequence. The RA2 will open the envelope for the individuals; with the information on the paper cards represent their group status. The same method will be used to randomize the subsequently recruited participants. Each block of individuals will have an independent computer-generated random sequence to determine the group assignment.

The participants will receive the assigned intervention within two weeks of baseline measure. They will not be informed about whether their received intervention is the tested one. For all individuals, the author ([name]) will measure perceived treatment credibility at the fifth week of training. This timeframe allows sufficient exposure to treatment before reporting expectations [2]. Another RA (RA3), who is blinded to the participants’ group status, will measure the mediating and outcome variables upon completion of the study intervention for all the study individuals.

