### Data processing and analysis

Data will be double-entered for validation and analyzed on an intention-to-treat (ITT) basis. Skewed variables will be transformed before being subjected to analyses. Baseline characteristics between the two arms of participants will be compared using t test, chi-square test or Fisher’s exact test, as appropriate. Mixed effects models will be used to compare the differential changes on the primary (sleep pattern and quality) and secondary (physical fitness and mood status) outcomes across the baseline and post-test (T2) between the two study arms, with adjustment for the potential control variables (i.e. expected treatment credibility, demographic and health profile) which are statistically non-equivalent at baseline (*p* < 0.25). In particular, a dummy variable (group) will be assigned to represent the exercise training group (i.e. treatment group) with the health education group (i.e. control group) as reference, and another dummy variable (time) will be set to indicate the time points (1 = post-test, 0 = pre-test) in the mixed effects model. To accurately identify the effects of the exercise training, an interaction term group × time will also be included in the model to assess the difference in the change of each outcome across the pre-test and post-test period (i.e. pre-post change) between the two study groups. The statistical significance of the model coefficients, including the interaction term, will be assessed by Wald test. The strengths of mixed effects model lie in accounting for intra-correlation between repeatedly measured data and accommodating missing data caused by dropout, provided the data are missing at random [26]. This method is most suitable for ITT analysis without the need for missing data imputation. All analysis will be conducted by using SAS release 9.3 (SAS Institute Inc, Cary, NC) at a 5% level of significance. Depending on the data distribution, the mixed effects modeling will be performed using the PROC MIXED or NLMIXED.

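### Optional gain in precision: the group × time model leaves the pre-randomisation baseline difference free, so it is less precise than a model that constrains or adjusts for the baseline outcome

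*Protocol article*

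**What the plan says.** Under Data processing and analysis, the primary and secondary outcomes are compared with mixed effects models over baseline and post-test. In these models "a dummy variable (group) will be assigned to represent the exercise training group", with health education as reference. A second dummy marks time, and "an interaction term group × time will also be included in the model to assess the difference in the change of each outcome". The effect of exercise is read from that interaction by a Wald test. The listed control variables are treatment credibility and the demographic and health profile, where they differ at baseline with p < 0.25. The baseline value of the outcome is not among them, and nothing sets the baseline means equal.

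Under Study design, outcomes and mediators are measured before randomisation. Under Method of randomization and data collection procedure, each block of participants "will be evenly randomized to the study arms in a block".

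The sample size (Study settings and participants) is for a pre-post design: "Power analysis is used to estimate the sample size estimation for pre-test–post-test study with attrition". The target is that "this study aims to detect a small to medium effect size of 0.4 on the primary sleep pattern and quality outcomes", and the article states that "n = 104 participants per study arm would give the study 80% power at a 5% level of significance", "assuming randomization will render the two arms equal at baseline and allowing for a 10% attrition". The number is then raised to 112 per arm for the path analysis ("112 × 0.9 = 100 per arm").

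**The concern.** The sizing assumes that the arms are equal at baseline, and randomisation after the baseline measurement makes this true in expectation. The analysis model nevertheless spends a parameter on a baseline group difference. With two time points and a free group effect, the interaction is the difference in mean change, so the noise of the baseline measurement enters the contrast in full. A model that treats the baseline means as common, or adjusts for the baseline outcome, removes only the part of that noise that predicts the post-test value.

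The listed covariates do not recover the loss. Entered as main effects in a two-time-point model with complete data, they leave the interaction unchanged.

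At stake is precision on the continuous sleep, fitness and mood outcomes. If the pre-post correlation turns out low, the margin over 80% power is at stake too.

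**Working it through.** **Inputs.** From the article: d = 0.4, 80% power, 5% level, 10% attrition, 104 then 112 per arm, 1:1 allocation. Assumed: two-sided test, equal variances at both times, d in units of the SD of a single measurement, dropout completely at random. The pre-post correlation ρ is not given, so a range is used. The only related figure is the CPSQI test–retest reliability of 0.77 (Sleep quality). It is not a 16-week correlation and serves only as an upper illustration.

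**1. The stated 104.** The base number is 2 × (1.960 + 0.8416)² / 0.4² = 98.1 per arm. A plain post-test comparison inflated for dropout gives 110 or 109, not 104. The article names RMASS2 but prints no formula. A pre-post contrast with attrition at the second time point needs

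98.1 × (1 + 1/0.9 − 2ρ/√0.9).

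- ρ = 0.5: 98.1 × 1.057 = 103.7, hence 104, as stated.
- ρ = 0.4: 124.4.
- ρ = 0.3: 145.1.

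The stated number therefore corresponds to the planned contrast at ρ = 0.5, a value obtained by solving backwards.

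**2. Variance with complete data.** In units of the single-measurement variance, the change contrast has factor 2(1 − ρ) and the baseline-adjusted contrast 1 − ρ². The ratio is (1 − ρ²) / (2(1 − ρ)) = (1 + ρ)/2.

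- ρ = 0.3: 0.65, a cut of 35%.
- ρ = 0.5: 0.75, a cut of 25%.
- ρ = 0.77: 0.885, a cut of 11.5%.

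The ratio is below 1 for every ρ < 1.

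**3. Variance with 10% dropout.** The planned mixed model also uses the baselines of dropouts, so it is slightly better than a change score in completers. With N randomised per arm, the likelihood variances of the effect are

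- planned: (2/N) × [(1 − ρ)² + (1 − ρ²)/0.9]
- constrained: 2(1 − ρ²) / (0.9 N)

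At N = 112 and ρ = 0.5 these are (2/112) × (0.25 + 0.8333) = 0.01935 and 1.5/100.8 = 0.01488. The ratio is 0.769, a cut of 23%.

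**4. Power at 112 randomised per arm** (noncentral t, about 200 degrees of freedom):

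| ρ | planned variance | constrained variance | planned power | constrained power |
|---|---|---|---|---|
| 0.3 | 0.02681 | 0.01806 | 68% | 84% |
| 0.4 | 0.02310 | 0.01667 | 75% | 87% |
| 0.5 | 0.01935 | 0.01488 | 82% | 90% |
| 0.7 | 0.01173 | 0.01012 | 96% | 98% |

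Planned power crosses 80% at ρ of about 0.48. Constrained power is still 80.7% at ρ = 0.

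**5. The scale of d.** If 0.4 is in units of the SD of change, the planned contrast has unit variance whatever ρ is, and its power does not depend on ρ. The article does not say which SD is meant.

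**The case against.** The strongest reply is that nothing here is wrong. Group × time is a valid test of the stated hypothesis of greater improvement than control, and the sample size was computed for the same contrast, so design and analysis agree. That stands: this is a choice between two valid models.

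Two stronger readings are tempting, and the article supports neither.

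- **That the planned analysis is biased**, because chance imbalance at baseline carries into the change through regression to the mean. Over randomisation the change estimator is unbiased, and chance imbalance is already part of its variance. The loss is one of efficiency only.
- **That the trial is underpowered.** At the ρ that reproduces 104, the plan gives about 82% with 112 per arm. A shortfall needs ρ below about 0.48 and d scaled by the single-measurement SD, and the article establishes neither. Nor is the absence of ρ a fault, since a condensed article may leave it to the full plan.

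It is also fair to say that the formulas are for continuous outcomes. The article allows NLMIXED where the distribution calls for it, and the number of awakenings is a count, for which the percentages do not carry over directly. Finally, under dropout the planned model is close to a change-score analysis but not identical with it; the power table allows for this.

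None of this removes the gain. For continuous outcomes the constrained model is more precise at every ρ below 1, and it rests on an equality that the design already guarantees.

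**Conclusion.** The point holds as an improvement available at almost no cost, not as an error. The planned model estimates a baseline difference that is zero by design and so gives up precision on the continuous outcomes. The variance cut from constraining or adjusting for baseline is 35% at ρ = 0.3, 25% at ρ = 0.5 (23% with the planned 10% dropout) and 11.5% at ρ = 0.77. At ρ = 0.5 power rises by about 8 percentage points (82% to 90%), and at ρ = 0.3 by about 16 (68% to 84%).

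These figures rest on an assumed ρ, equal variances and, for the powers, d in single-measurement SD units. They show protection against a low correlation; they do not show that the plan misses its stated power.

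**What to change.** Under Data processing and analysis, for continuous outcomes, fit the mixed model with time and group × time but without the group main effect, with an unstructured 2×2 covariance. The baseline mean is then common to both arms and the interaction coefficient is the group difference at post-test; report that as the effect. ANCOVA of the post-test value on the baseline value is the alternative. The constrained mixed model keeps all randomised participants with a baseline and the missing-at-random property that the article values.

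For outcomes analysed by NLMIXED, such as the number of awakenings, include the baseline value as a covariate or constrain the baseline in the same way.

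The cost is a small change to the model statement, made before the outcome data are analysed by arm. No extra data or participants are needed.

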### Study interventions

#### The 16-week moderate-intensity endurance exercise

The moderate-intensity endurance exercise training will be conducted by a research assistant with baccalaureate training in physical education or sport medicine (RA1). The co-authors ([name]) who are academicians in physiotherapy and exercise physiologist will conduct a three-day training course for the RA1. The exercise training is designed according to the recommendations of the American College of Sports Medicine (ACSM)’s position stand on Exercise and Physical Activity for Older Adults [20]. It is a moderate-intensity 7.5-cm-high bench stepping exercise program for seniors. It is a 16-week program, with three 60-min group training sessions (group size of around ten participants) per week. Each session starts with a 10-min warm-up period using stretching exercise and stationary mobilizing exercise for trunk and limb joints at both upper and lower bodies (e.g. shoulders, elbows, wrists, hips, knees, and ankles) and followed by a session of moderate-intensity endurance exercise. The duration of the endurance exercise will increase gradually from 20 min to the targeted 40 min over four weeks. The endurance exercise includes bench stepping exercise using a 7.5-cm-high stable wooden platform. This exercise has been shown to be very suitable for older people who are less physically active or have reduced joint flexibility and reduced bone strength [21]. Individuals will perform the bench stepping exercise in bouts of at least 10 min each (with a maximum of 5 min of rest in between the exercise bouts) to reach the targeted duration (i.e. 40 min of endurance exercise). Close monitoring and verbal encouragement will be provided by the attending RA1. Moderate-intensity exercise has been widely used among older people and is even safe for older patients with chronic diseases [22]. The Borg Rate of Perceived Exertion (Borg RPE) will be used to monitor the exercise intensity [23]. This is a 15-point scale with scores in the range of 6–20. Descriptors are attached throughout the scale with higher scores indicating more perceived exertion. Physical activity that results in a rating of 12–14 (descriptor: “somewhat hard”) on the Borg RPE is identified as reaching a moderate intensity [23]. The RA1 will explain the Borg RPE scale to the participants and instruct them to speed up or slow down their movements in order to achieve a feeling of “somewhat hard” at the Borg RPE rating of 12–14. The training session will end with a 10-min cool down session with walking exercise and stationary trunk and limb mobilizing exercise involving the joints of the shoulders, elbows, wrists, hips, knees, and ankles. The training will follow the ACSM safety guidelines with assessment done on blood pressure (BP) and heart rate (HR) and contradictory symptoms before training. Attendance rate and adverse events will be recorded.

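### Classes of about ten are taught together for 16 weeks, but the sample size and the mixed model allow only for correlation within a person, so any positive class correlation raises the type I error above 5% or lowers power

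*Protocol article*

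**What the plan says.** **Delivery.** The exercise section specifies "three 60-min group training sessions (group size of around ten participants) per week", running for 16 weeks. The education section specifies weekly one-hour sessions and gives no class size. Table 1, on compliance, treats both programmes as classes: each has a title and badges, sets a joint attendance goal, sees its attendance posted, and is encouraged to socialize.

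**Randomization.** It is individual. Each successive set of about 20 recruits "will be evenly randomized to the study arms in a block", so a block yields about ten people per arm.

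**Sample size** (Study settings and participants). The text says "this study aims to detect a small to medium effect size of 0.4" and that "n = 104 participants per study arm would give the study 80% power at a 5% level of significance", "assuming randomization will render the two arms equal at baseline and allowing for a 10% attrition". No ICC or design effect appears. The increase from 104 to 112 per arm is explained by structural equation modelling.

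**Model** (Data processing and analysis). The terms are arm, time, arm × time and selected covariates, tested by Wald tests. The only correlation mentioned is the one in "The strengths of mixed effects model lie in accounting for intra-correlation between repeatedly measured data". The two clusters in the path analysis are the two time points, not classes.

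**The concern.** Randomization makes the arms comparable at baseline, but it does not keep participants independent afterwards. People who train together up to three times a week for 16 weeks, under a scheme designed to build group cohesion, can come to share attendance, effort and mood. Mood is also one of the hypothesized mediators. A shared class effect at post-test adds to the variance of the arm difference and does not average out over individuals, only over the roughly 11 classes per arm.

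A model whose only dependence is within person does not see this component. At stake are the 5% error rate of the primary comparison, the width of its interval, and the power claim. The bootstrap intervals for mediation have the same weakness if they resample individuals.

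**Working it through.** **Inputs from the protocol article:** d = 0.4; 80% power; 5% significance (two-sided assumed); 10% attrition; 104 per arm raised to 112; exercise classes of about 10; blocks of about 20 split evenly.

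**Assumed, because not stated:** ICC 0.01 to 0.10, on the scale of the pre-post change; education classes also of 10; d on the scale of the contrast analysed.

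**Step 1. Reproduce the plan's figure.** With independent participants, n = 2(1.96 + 0.842)²/0.4² = 98.1 completers per arm. The usual inflation, 99/0.9, gives 110. Averaging retention over the two time points (100% and 90%, mean 95%) gives 98.1/0.95 = 103.3, so 104. That use of attrition is my inference. As a power check, 104 × 0.9 = 93.6 completers gives 78.1%, and the planned 112 × 0.9 = 100.8 gives 81.1%. The stated size is thus reproduced with a design effect of 1.

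**Step 2. Add class.**
- Design effect: DE = 1 + (10 − 1) × ICC.
- Type I error if class is ignored: 2[1 − Φ(1.96/√DE)].
- Power if class is modelled, from the design effect alone: Φ(0.4√(100.8/(2DE)) − 1.96).
- Power with class-level degrees of freedom: noncentral t on 22 − 2 = 20 df (about 11 classes per arm).

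Example, ICC 0.05: DE = 1.45. 1.96/√1.45 = 1.628, so type I error is 10.4%. 100.8/1.45 = 69.5 and 0.4√(69.5/2) = 2.358, so power is Φ(0.398) = 65.5%.

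| ICC | DE | Type I error, class ignored | Power, DE alone | Power, 20 df |
|---|---|---|---|---|
| 0 | 1.00 | 5.0% | 81.1% | 77.1% |
| 0.01 | 1.09 | 6.0% | 77.6% | 73.5% |
| 0.02 | 1.18 | 7.1% | 74.4% | 70.1% |
| 0.05 | 1.45 | 10.4% | 65.5% | 61.2% |
| 0.10 | 1.90 | 15.5% | 54.0% | 50.0% |

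A simulation with 11 classes of 9 completers per arm gave type I errors of 6.0%, 6.8%, 9.7% and 14.4% when class was ignored. A test on class means held about 5% throughout.

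**Step 3. Break-even.** 100.8/98.1 = 1.027, and 0.027/9 = 0.003. Measured against the stated 104 instead, (112/104 − 1)/9 = 0.009.

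**Step 4. Sensitivity.**
- Only the exercise arm clusters, ICC 0.05: DE = (1.45 + 1)/2 = 1.225, type I error 7.7%, power 73%.
- Completers per class 100.8/11 = 9.2, ICC 0.05: DE = 1.41, type I error 9.9%.
- d and ICC both on the post-score SD, pre-post correlation 0.7, ICC 0.02: the change variance is 2(1 − 0.7) = 0.6, and with class 0.6 + 9 × 0.02 = 0.78. Power is about 87% even on 20 df. But the variance ratio is 0.78/0.6 = 1.3, and 1.96/√1.3 = 1.719, so ignoring class gives a type I error of about 8.6%.

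**The case against.** **The model is not fully specified.** The sentence on the strengths of mixed models describes a general property. The article lists fixed terms and software but no random-effects structure, and such detail is often left to an analysis plan. This carries some weight for the degrees-of-freedom method. It does not remove the point. The article fixes the model terms, the test and the power claim, names one source of correlation, and plans a measure of intervener characteristics for possible adjustment while saying nothing of class. Carried out as described, the analysis gives a standard error that is too small whenever the class ICC is positive.

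**The ICC may be small.** One role teaches all exercise classes and another all education classes, so differences between teachers do not create between-class variation within an arm. The two classes from a block share time and recruitment, and those shared effects largely cancel in the arm difference. Both are fair reasons to doubt the upper end of the range. Neither makes the ICC zero.

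**Stronger readings that the documents do not support.**
- A reader might infer that 80% power needs an ICC of exactly zero. There is slight slack, to about 0.003.
- A reader might attribute the 20-df power figures wholly to clustering. About 4 points come from the degrees of freedom, since power on 20 df is 77.1% even at ICC 0.
- A reader might add the two consequences together. They are alternatives: ignoring class mainly inflates the type I error, and modelling it exposes the power loss.
- A reader might take it as established that the trial is underpowered. The ICC, the education class size, the SD scale of d and the pre-post correlation are all unstated, and a favourable combination restores power.

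**Conclusion.** The point stands in conditional form. Group delivery in the exercise arm and the lack of any clustering allowance in the sample size are stated facts. Class delivery of education is a reasonable inference from Table 1, and its class size from the blocks of 20. The direction is certain for any positive class ICC: the planned arm-by-time test exceeds 5%.

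The size depends on an ICC that the document does not give. It runs from modest at 0.01 to serious at 0.10. It is smaller if only the exercise arm clusters. Power, though not the type I error, improves if d is on the post-score SD and the pre-post correlation is high. The claim that the sample "would give the study 80% power at a 5% level of significance" cannot be left unconditional.

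**What to change.** - **Data:** record each participant's class in both arms. The article says recruitment is ongoing, so this should still be possible.
- **Model:** add a random class effect acting at post-test (class × time). A class intercept common to both time points would cancel from the pre-post change and leave the standard error uncorrected. Use small-sample degrees of freedom, such as Kenward-Roger, in place of the plain Wald test. A block main effect is optional and adds little to the arm × time contrast.
- **Mediation:** resample whole classes in the bootstrap.
- **Sample size text:** state an assumed ICC range, the class size in each arm, and the SD scale of d, and give power across that range.

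The cost is wording, one extra variable, wider intervals and a less favourable stated power. It needs no extra participants, but it corrects the error rate and does not restore 80% power. Under the main assumptions, restoring it would need 98.1 × DE/0.9 enrolled per arm: 119, 129, 159 or 208 at ICC 0.01, 0.02, 0.05 or 0.10.

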Path analysis is used to examine the mediating roles of physical fitness and mood status on the effect of exercise training on sleep pattern and quality with adjustment for the above control variables. Based on our hypothesized mediation model (Fig. 1), a baseline path model using the baseline data will be built first. To which path model with the same structure for T2 is added and linked by intra-correlations among the same variables. The final mediation model will then consist of two clusters (corresponding to the two time points) and are linked by the intra-correlations. The equality of a specific path coefficient in the two clusters can be assessed by imposing equality constraint on the coefficient and tested using a nested goodness-of-fit test [27]. The mediation effects of physical fitness and mood status on the effect of exercise training on sleep pattern and quality will be assessed through the significance of the corresponding products of indirect path coefficients from exercise training to sleep pattern and quality, respectively [28]. In view of the possibility of violation of normality assumption, a bootstrapping approach [28], instead of the conventional multivariate delta method, will be used to estimate the standard errors and the confidence intervals of the product terms (mediation effects). Furthermore, the effect of exercise training (as compared to control) on the change of the path coefficients to the sleep pattern and quality outcomes directly or by way through the mediators (physical fitness and mood status) over time can be assessed using the three-way interactions approach [27]. The path analyses and the bootstrapping will be performed using Mplus Version 6 and the parameters will be estimated by mean and variance adjusted weighted least square method (WLSMV). The bootstrapping estimations of the standard errors and confidence intervals will be performed using bias-corrected bootstrapping method with 10,000 replications [28]. The overall fit of the path models is assessed using comparative fit index (CFI), root mean square error of approximation (RMSEA), and standardized root mean square residual (SRMR), with CFI > 0.95, RMSEA < 0.06, and SRMR < 0.08, indicating a good data-model fit [27].

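### The mediation path model is fixed to WLSMV, which needs a stricter missing-data assumption than the mixed model on the same data and can bias the mediated effect in either direction

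*Protocol article*

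**What the plan says.** All references are to the protocol article.

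- **Analysis basis** (Data processing and analysis): "Data will be double-entered for validation and analyzed on an intention-to-treat (ITT) basis".
- **Mixed model** (same section): its merits include "accommodating missing data caused by dropout, provided the data are missing at random", and the text adds: "This method is most suitable for ITT analysis without the need for missing data imputation". Both remarks concern the mixed model.
- **Path model** (same section): "The final mediation model will then consist of two clusters (corresponding to the two time points) and are linked by the intra-correlations". It is fitted "with adjustment for the above control variables", and the estimator is fixed: "the parameters will be estimated by mean and variance adjusted weighted least square method (WLSMV"). Indirect effects get bias-corrected bootstrap intervals with 10,000 replications. No missing-data assumption is given for this model.
- **Attrition** (Study settings and participants): 112 per arm are randomised "to attain the recommended total sample size of 200 participants (i.e. 112 × 0.9 = 100 per arm").

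**The concern.** Both analyses use the same sleep, fitness and mood measurements, with the same expected dropout. The mixed model is likelihood-based, so a participant with only a baseline value still contributes, and dropout that depends on that value is allowed for.

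WLSMV works from univariate and bivariate moments. In the two-cluster structure, baseline sleep, mood and fitness are outcomes of the first cluster and not predictors of the second. A dropout's baseline values inform the baseline moments but not the post-test paths from exercise to mediator and from mediator to sleep. Those paths come from people with post-test data. Dropout that depends on group or on the adjusted covariates is still accommodated. Dropout that depends on baseline sleep, mood or fitness is not.

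At stake is the second hypothesis, that fitness and mood mediate the effect. Arm-specific dropout is plausible because the burdens differ: three exercise sessions a week against one talk.

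**Working it through.** **1. The plan's own figure.** 100 / 0.9 = 111.1, rounded up to 112 per arm. 112 × 0.9 = 100.8 per arm, or 201.6 in total. Expected without a post-test: 224 × 0.1 = 22.4. The figure reproduces.

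**2. Is an ordered-categorical estimator needed?** The named variables are total sleep time, sleep latency, number and duration of awakenings, sleep efficiency, CPSQI, predicted VO2max and POMS-SF. These are scores, continuous measures and one count. Non-normality is already addressed by transforming skewed variables and by the bootstrap. The bootstrap repairs intervals; it does not remove selection bias from a point estimate.

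**3. Size of the shift.** The document gives no correlations and nothing on who drops out, so every input below is assumed except the 10% attrition and the total effect of 0.4 SD ("this study aims to detect a small to medium effect size of 0.4 on the primary sleep pattern and quality outcomes"). Estimation from participants with post-test data stands in for WLSMV, which was not run itself. The comparator is maximum likelihood using every baseline. Indirect effect = a × b, where a is the exercise-to-mediator path and b the mediator-to-sleep path.

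*Set A: mood as mediator.* Correlations are 0.6 (same variable over time), 0.4 (mood with sleep) and 0.3 (cross-lagged), with 2,000,000 simulated participants. True total effect −0.40, true indirect effect −0.12. Odds ratios (OR) are per SD of each of baseline mood and sleep, with worse status leaving more. Dropout is given as exercise/control.

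| Dropout | Total, post-test only | Indirect, post-test only |
|---|---|---|
| 10%/10%, unrelated to baseline | −0.40 | −0.119 |
| 10%/10%, OR 2, exercise arm only | −0.45 (+12.5%) | −0.140 (+17%) |
| 15%/5%, OR 2, both arms | −0.45 (+12.5%) | −0.136 (+13%) |
| 15%/5%, OR 3, exercise arm only | −0.51 (+27.5%) | −0.155 (+29%) |
| Selective loss of worse controls | −0.35 (−12.5%) | −0.097 (−19%) |
| Same dependence and rate in both arms | −0.40 (0%) | −0.116 (−3%) |

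Percentages are estimate / truth − 1, for example 0.155 / 0.12 − 1 = 0.29. Maximum likelihood gave −0.40 and −0.12 throughout.

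*Set B: fitness as mediator.* a = 0.4, b = −0.4, direct effect −0.24, so the indirect effect is −0.16 and the total −0.16 − 0.24 = −0.40. Pre-post correlation is 0.5 or 0.7, with 1,000,000 participants. Change in the indirect effect from post-test-only estimation:

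- less-fit participants leave the exercise arm, 10%/10%, OR about 2: +8.7% and +11.7%;
- 15%/5%, same dependence in both arms: +8.0% and +11.4%;
- less-fit controls leave, 10%/10%: −8.2% and −11.9%;
- fitter exercisers leave, 10%/10%: −8.2% and −12.0%;
- same dependence on fitness and same rate in both arms: +0.2% and −0.1%;
- extreme case, 20%/0%, OR about 4.5: +28.2% and +39.9%.

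Maximum likelihood stayed within 0.4% of the complete-data value in every scenario.

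**4. Against sampling error.** With the Set B values and 100 per arm, the sampling SD of the indirect effect is 0.063, or 0.063 / 0.16 = 39% of its size. A moderate shift is 0.1780 − 0.1594 = 0.0186, and 0.0186 / 0.063 = 0.30 SD. The extreme case is 0.2234 − 0.1596 = 0.0638, about one SD.

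**The case against.** **No textual contradiction.** Missing at random is claimed for the mixed model only, and the path model makes no missing-data claim. That is right: the issue is that two analyses of the same data rest on different assumptions. Missing-data handling for a secondary analysis may also be left to an analysis plan that is not shown, and multiple imputation before WLSMV would restore missing at random. That could rescue the choice, but the estimator itself is fixed here.

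**WLSMV may be wanted.** The model figure is not shown, CPSQI and POMS-SF are built from ordinal items, and the authors foresee non-normality. This has some force. It is why imputation followed by WLSMV is acceptable if ordered categories are modelled, and why fit statistics need care under normal-theory likelihood.

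**The effect is small and rests on assumptions.** This stands for moderate scenarios, as does the fact that completers served as a proxy for WLSMV.

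Four stronger readings are tempting but unsupported:

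- *Mediation will be overstated.* The direction depends on who leaves which arm, and the document is silent on that.
- *Baseline data are discarded.* They stay in the baseline cluster; they are only unused for the post-test paths.
- *The sample-size text plans a completers' analysis.* It is an ordinary attrition allowance, and the primary calculation makes the same one.
- *Likelihood estimation would make the path-model effect equal the primary result.* The primary effect is a group × time change and the path effect is a post-test path, so chance baseline differences can separate them under any estimator.

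**Conclusion.** The point holds for the secondary mediation aim only; the primary comparison is untouched. The stated estimator makes the mediation result depend on dropout being unrelated to baseline sleep, mood and fitness beyond group and covariates, or acting alike in both arms. The mixed model does not need that. With 10% attrition and arm-specific selection, the illustrative bias is about 10–30% in either direction, usually below one sampling SD. It reaches about 40%, or one SD, only in the most extreme case, and is near zero when dropout acts alike in both arms. These sizes rest on assumed correlations and dropout mechanisms and on post-test-only estimation as the proxy. The mechanism follows from the estimator and the two-cluster structure; the document does not describe it.

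**What to change.** In Data processing and analysis, replace WLSMV by full-information maximum likelihood in Mplus, include all randomised participants with baseline data, and keep the bias-corrected bootstrap for the indirect effects. Add a sentence that the path model assumes missing at random, as the mixed model does. If ordered-categorical variables are in fact modelled, multiple imputation before WLSMV is an acceptable alternative.

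The cost is an estimator setting and a sentence or two, with the same software and data. Run time is somewhat longer. If variables stay non-normal after transformation, the fit indices and nested tests need a robustness check, such as robust maximum likelihood or a bootstrap fit test.
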